# Healthy school recognized campus: design and methodology of a hybrid type 2 implementation-effectiveness cluster randomized trial

**DOI:** 10.1186/s13012-026-01487-2

**Published:** 2026-02-05

**Keywords:** Body mass index, Exercise, Nutrition, Adolescent health, Health education, Cooperative extension, Implementation strategy, Obesity

## Abstract

**Background:**

About one-third of U.S. youth are overweight and most have at least one risk factor that increases their chance of developing cardiovascular or other chronic diseases. School- and research-based physical activity and healthy eating programs can reduce obesity and improve health outcomes; however, schools face many implementation challenges. Healthy School Recognized Campus (HSRC) bundles school- and researched-based programs to improve their implementation and student health outcomes. This paper describes the protocol for a hybrid type 2 implementation-effectiveness, cluster dual randomized controlled trial that evaluates the (aim 1) effectiveness of the HSRC initiative for improving health behaviors and (aim 2) the impact of an implementation strategy – school-to-school mentoring – on HSRC’s delivery.

**Methods:**

Students in 4th through 9th grade (*n* = 500) at public schools (*n* = 20) across East and Central Texas will be randomized at the school level to determine the effectiveness of HSRC (vs. waitlist control condition) on BMI z-score (primary outcome), physical activity measured via accelerometer, and skin carotenoids (i.e., fruit and vegetable intake; secondary outcomes). Assessments will occur at the start and end of one school year. Program implementers (*n* = 200) at schools will be randomized to assess the impact of the school-to-school mentoring strategy (vs. standard implementation) on HSRC’s acceptability, appropriateness, and feasibility (co-primary outcomes). Assessments will occur at the start, middle, and end of one school year. The assessment at the end of the school year will also include a concurrent mixed-methods approach (QUAL + QUAN), guided by the Consolidated Framework for Implementation Research (CFIR), to evaluate the school-to-school mentoring strategy. For quantitative outcomes, a generalized linear model framework will be used to evaluate HSRC and the school-to-school mentoring strategy.

**Discussion:**

This study’s innovative dual randomized design allows for rigorous assessment of HSRC on effectiveness outcomes and the evaluation of a school-to-school mentoring implementation strategy on implementation outcomes. If both HSRC and the school-to-school mentoring strategy have their hypothesized effect, we will be well positioned to address cardiovascular and other chronic disease risk factors among youth using a scalable, widely used approach within one of the largest health educator networks in the country.

**Trial registration:**

Clinicaltrials.gov on July 1, 2025 (NCT07079995).

**Supplementary Information:**

The online version contains supplementary material available at 10.1186/s13012-026-01487-2.

Contributions to literature
This study advances implementation science through its novel use of a hybrid type 2, cluster dual randomized controlled trial, providing feedback about the acceptability and feasibility of this design in community settings.The school-to-school mentoring strategy was iteratively refined in partnership with Extension agents (i.e., community health educators), demonstrating how iterative refinement can lead to an implementation strategy that is ready to be evaluated via a clinical trial.Concurrent testing of an intervention and an implementation strategy via two clinical trials will provide rigorous evidence that can be used to further inform the use of Extension’s evidence-based health promotion programs.

## Background

Obesity rates among children and adolescents in the United States continue to climb, with nearly 1 in 5 children being classified as obese [1, 2]. Obesity has major impacts on a child’s health by affecting their cardiovascular and other chronic disease risk – often contributing to or creating additional comorbidities [3, 4]. Physical activity and healthy eating are critical behaviors for addressing obesity [5–7], and they provide additional physical and psychological health benefits (i.e., reduced anxiety and depression) [8–10]. However, recent data show that only about a quarter of children and adolescents meet the United States physical activity guidelines of 60 min per day, and physical activity has continued to decline over the past decade as sedentary behaviors and screen time have risen [11, 12]. Similarly, 49% of children have overall poor diet quality, which often consists of empty calories (e.g., soda, enriched grains), is high in sodium and sugar, and lacks fruits and vegetables [13, 14]. Research-based programs that effectively improve physical activity and healthy eating are valuable tools for addressing childhood obesity.

National public health agencies strongly recommend, and some states’ laws require, the delivery of one or more research-based programs within schools [15–17]. These programs are a common way that health educators aim to promote physical activity and healthy eating and reduce obesity among children and adolescents [15–17]. Schools are an ideal setting for early interventions, as they can establish healthy physical activity and dietary behaviors early in life [18]. Despite the substantial potential of schools for promoting health, critical barriers to implementing health promotion programs in schools persist, including staff-related challenges (e.g., negative attitudes, limited teacher time, insufficient training), student-related factors (e.g., low motivation, limited engagement), constrained resources (e.g., funding and personnel), and competing curricular priorities [19–22]. Addressing these barriers through implementation strategies – methods to enhance program delivery – is essential for translating research-based programs into meaningful health outcomes and for ensuring that programs are both feasible and scalable within the school setting [21, 23].

The Healthy School Recognized Campus (HSRC) initiative directly addresses these implementation challenges by offering a structured framework for schools to adopt and deliver multiple research-based physical activity and nutrition programs [24–27]. Rather than relying on a single curriculum, HSRC bundles complementary programs that collectively support healthier behaviors within the school environment [24–27]. Participating schools commit to implementing at least three research-based physical activity and/or nutrition programs, including: (1) an 8-week walking challenge [28–30], (2) at least one additional program for youth, and (3) at least one program for caregivers, such as parents and/or school staff. A defining strength of HSRC is its multilevel design that aligns with ecological frameworks for health [7, 31, 32]. More specifically, HSRC aims to help health educators who use it engage individuals (i.e., intrapersonal level), social networks (i.e., interpersonal level), and school support (i.e., organizational level) in delivering programs. Schools that complete HSRC also receive public acknowledgement via a banner and/or proclamations during school board meetings, which aligns with prior research showing that such recognition can support improvements in student health outcomes, including body mass index (BMI) [8].

Previous studies have evaluated the effects of the HSRC initiative on student health outcomes and the impact of implementation support strategies on HSRC’s delivery [24–27]. Preliminary data from a single-group pre- to post-test pilot study showed several promising, positive effects of HSRC on the physical activity, nutrition, and BMI z-scores of students [27]. However, a more rigorous study design is needed to better evaluate whether these outcomes are related to HSRC or to other factors occurring during the same period (e.g., the start of the school year) [33]. Similarly, previous work evaluating three different implementation strategies – additional incentives, engaging contests, and school-to-school mentoring – demonstrated that the school-to-school mentoring strategy was a promising approach to improving HSRC’s short-term implementation outcomes (e.g., acceptability, appropriateness, and feasibility) [24]. Nevertheless, it has not been evaluated compared to HSRC’s standard implementation process. As a result, additional rigorous randomized controlled trials are needed.

This paper describes the protocol for a hybrid type 2 implementation-effectiveness, cluster dual randomized controlled trial (DRCT). DRCTs include two randomized controlled trials embedded in the same study. The first embedded randomized controlled trial evaluates: (aim 1) the effectiveness of the HSRC initiative for improving health behaviors (physical activity and healthy eating) and outcomes (BMI z-score) compared to a control group. The second embedded randomized controlled trial evaluates: (aim 2) the impact of an implementation strategy – school-to-school mentoring – against standard implementation on implementation outcomes (acceptability, appropriateness, feasibility). Concurrently conducting two randomized controlled trials to address these aims represents an innovative approach to advancing research on effective school-based approaches to reduce obesity and other chronic disease risk factors.

## Methods

### Study setting and school recruitment

The Central and East regions of Texas have some of the highest rates of cardiovascular disease and stroke mortality in the United States [34]. Accordingly, we will recruit ten schools from these regions in year one and ten schools in year two to participate in this study. As HSRC is a Texas A&M AgriLife Extension initiative and given the Cooperative Extension systems’ ability to bridge the gap between universities and communities [35], we will work with AgriLife county Extension agents (i.e., health educators) to assist with recruiting and implementing programs in schools.

We will use Texas Education Agency data to identify public schools of similar size, rurality, socioeconomic status, and racial/ethnic composition that are either eligible for HSRC or have previously contacted AgriLife Extension expressing interest in participation [36]. Once schools are identified, a research staff member – with or without the help of a county Extension agent – will contact interested schools via phone call, email, informational presentations, and/or flyers to share information about the HSRC initiative and the study. Schools that express interest in participating will meet with the research team to review study expectations and procedures. If the school agrees to participate in the study, a school representative will sign a memorandum of understanding agreeing to participate and a site authorization to allow data collection at the school.

### Study design

This study uses a hybrid type 2 implementation-effectiveness, cluster dual randomized controlled trial (DRCT; Fig. 1). DRCTs include two randomized controlled trials within the same study: one testing the intervention (i.e., HSRC) and one testing an implementation strategy [37–39]. DRCTs allow for rigorous testing of both the effectiveness of an intervention and the impact of an implementation strategy on outcomes, accelerating the translation of interventions into practice [37–39]. For the effectiveness aim (Aim 1), we will compare outcomes in ten Texas schools that receive HSRC with ten waitlist control schools (Fig. 1 in gray). For the implementation aim (Aim 2), ten schools will be randomized to receive a school-to-school mentoring program, and ten will receive standard implementation of the program (Fig. 1 in blue).

**Fig. 1 Fig1:**
[figure not shown]
Randomization for the Cluster Dual-Randomized Controlled Trial

### Procedure

#### Randomization

Schools will be randomized to receive one of four conditions: (1) immediate intervention and standard implementation (HSRC + SI), (2) immediate intervention and school-to-school mentoring (HSRC + M), (3) waitlist control and standard implementation one year later (WC + HSRC + SI), or (4) waitlist control and school-to-school mentoring one year later (WC + HSRC + M). To ensure balance across years, schools will be blocked into two cohorts of ten schools, with five receiving immediate intervention and five receiving waitlist control in each of the first two years. Additionally, three schools will receive standard implementation in year one, five in year two, and two in year three, whereas two schools will receive school-to-school mentoring in year one, five in year two, and three in year three (Fig. 1). The order of the ten conditions available each year will be randomized, and schools will receive them based on the order in which they enroll in the study (i.e., signed memorandum of understanding).

#### Student eligibility and recruitment

Irrespective of the school’s randomized conditions, student recruitment will occur at the beginning of the school's first year of enrollment. Recruitment strategies will include both online (e.g., email) and in-person outreach (e.g., back-to-school events). To be eligible to participate, students must be enrolled in 4th through 9th grade, be between 8 and 16 years of age, and be able to speak, read, and write in English. Students with impairments (e.g., motor, cognitive) or health conditions (e.g., pregnant) that would prevent completion of study assessments will be excluded. Caregivers will complete a consent form and a brief demographic survey at baseline. To consent for the student, caregivers must be at least 18 years old. Students will provide in-person assent before assessments. Students who decline to participate in the study or who are not enrolled by their caregivers will still be encouraged to engage in HSRC programming.

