This study further advances implementation science through its use of a hybrid type 2, cluster DRCT, which allows for simultaneous evaluation of both the effectiveness of the intervention (i.e., HSRC) and the impact of the implementation strategy (i.e., school-to-school mentoring) on outcomes [37–39]. By randomizing schools to HSRC or waitlist control, and to different implementation conditions, this study provides a unique opportunity to link improvements in HSRC’s implementation to changes in students’ health behaviors and outcomes. Additionally, the use of randomization to answer both implementation and effectiveness questions reduces selection bias, balances measured and unmeasured confounders across schools, and enhances the validity of causal inferences within both trials [73]. Furthermore, as both aims have adequate statistical power to detect small-to-moderate effects, our design makes efficient use of resources to conduct two randomized trials answering important questions that can help to close the research-to-practice gap.

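### Students are recruited after their school's condition is assigned, with no concealment described, so who enrols can differ between HSRC and waitlist schools

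*Protocol article*

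**What the plan says.** For Aim 1, students "will be randomized at the school level to determine the effectiveness of HSRC" (Abstract, Methods). The school joins first. Under Study setting and school recruitment, "a school representative will sign a memorandum of understanding agreeing to participate and a site authorization to allow data collection at the school". Under Randomization, the ten conditions available each year are put in random order, and "schools will receive them based on the order in which they enroll in the study (i.e., signed memorandum of understanding".

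Students come next. Under Student eligibility and recruitment, the article says that, irrespective of the school's "randomized conditions, student recruitment will occur at the beginning of the" school's first year of enrollment. The method is open outreach: "Recruitment strategies will include both online (e.g., email) and in-person outreach (e.g., back-to-school events". Enrolment depends on family choice: "Caregivers will complete a consent form and a brief demographic survey at baseline", and students then assent in person. Those who decline or are not enrolled "will still be encouraged to engage in HSRC programming".

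Two other sections bear on whether the arm can be seen. The Aim 1 conditions section has immediate schools receive HSRC at once and waitlist schools keep their existing programs unchanged. The Aim 2 conditions section sends mentoring schools a welcome email straight after randomization.

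The Discussion says that randomization "reduces selection bias, balances measured and unmeasured confounders across schools", and that it strengthens causal inference in both trials.

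**The concern.** Randomizing schools makes the schools comparable. It makes the measured students comparable only if they are identified before the condition is known, or in a way the condition cannot influence. Here the target is 25 volunteers per school from grades 4 to 9, found after the school's condition has been fixed. If the program year attracts a different kind of family or class from the one a waitlist year attracts, the arms can differ at entry in motivation, family support or expected trajectory.

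That difference would enter the primary outcome (BMI z-score) and both secondary outcomes (accelerometer activity and skin carotenoids). It could not be repaired once enrolment had closed.

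**Working it through.** **Order of events.**

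1. The memorandum is signed and the school takes the next condition on the list (Study setting and school recruitment; Randomization).
2. Students are recruited at the start of the school's first year, when the article already speaks of randomized conditions (Student eligibility and recruitment).
3. Baseline is measured between August 1 and November 30 (Outcomes).

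No single sentence says that assignment precedes student recruitment. It is a strong inference from these sections, and nothing in the article contradicts it.

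**What the stated safeguards do.**

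- Recruiting irrespective of condition equalizes the timing of recruitment. It does not determine who volunteers.
- The model adjusts each outcome for its own baseline, treats school as the cluster and adds covariates found in bivariate analyses (Statistical analysis). This removes measured differences in level, but not unmeasured differences in trajectory.
- Multiple imputation under intention-to-treat deals with missing outcomes among enrolled students, not with who enrolled.

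**Size, as an illustration.** The plan gives no figure for this bias to reproduce, and no ICC or SD for Aim 1. Two inputs come from the Power analysis: 447 students and 20 schools. The ICC (0, 0.02, 0.05) and the residual between-arm difference b are assumptions.

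- Mean school size: m = 447/20 = 22.35.
- Design effect: DE = 1 + (m − 1) × ICC = 1 + 21.35 × ICC, giving 1.000, 1.427 and 2.068.
- Standard error in SD units, two equal arms: SE = √(4 × DE/447), giving 0.0946, 0.1130 and 0.1360.
- Difference detectable with 80% power: (1.96 + 0.84) × SE, giving 0.265, 0.317 and 0.381 SD.
- Two-sided type I error when HSRC has no effect: Φ(−1.96 + b/SE) + Φ(−1.96 − b/SE).

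| Residual difference b | ICC 0 | ICC 0.02 | ICC 0.05 |
|---|---|---|---|
| 0.02 SD | 0.055 | 0.054 | 0.052 |
| 0.06 SD | 0.097 | 0.083 | 0.073 |
| 0.10 SD | 0.185 | 0.143 | 0.114 |

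Each b is a difference in the share of some type of family multiplied by that type's outcome advantage:

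- 0.02 SD: a 10-point gap in share × 0.2 SD.
- 0.06 SD: a 20-point gap (60% against 40%) × 0.3 SD.
- 0.10 SD: a 20-point gap × 0.5 SD.

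The middle case is 0.06/0.381 = 16% to 0.06/0.265 = 23% of the detectable difference. With the 475 students left after 5% loss (500 × 0.95), b = 0.10 SD gives 0.193, 0.147 and 0.116. The sign of b does not affect these error rates.

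**The case against.** The strongest reply is that the article says how a school gets its condition, not when the school, the agent, recruiters or families learn it. The mentoring email concerns Aim 2. Disclosure timing and recruitment scripts are details that an article commonly leaves to the full protocol. This stands against any statement that families know their arm. A reader might infer that waitlist families know nothing will happen that year, but no section says so. It does not dispose of the point: the stated sequence puts recruitment after assignment, and the arm shows in the school's own activities.

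Second, enrolment is not the gateway to HSRC. Students outside the study are encouraged to take part, the walking program is schoolwide, and waitlist schools are offered HSRC the following year. Enrolment brings measurement and a $20 item at each time point, with no difference by arm stated. This weakens the pull to enrol. It does not rule out an effect of publicity or staff engagement in the schools that are running programs.

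Third, a reader might infer that the bias favours HSRC. The documents do not support a direction. A waitlist school might draw only its most health-minded families while HSRC publicity brings in a broader group, which would bias against HSRC.

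Fourth, a reader might take the Discussion's sentence on balance to be false. It speaks of balance across schools, and for schools it is right.

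Fifth, baseline adjustment and the collected demographic, behavioural and fitness data offer real, if partial, mitigation. The mild case in the table is close to nominal.

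**Conclusion.** The point holds as a weakness of the design sequence: differential enrolment is possible, no protection against it is described, and the planned model would remove only part of it. It is not shown that enrolment will differ or which arm would gain.

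The size is unknown. The range of about 5% to 19% for type I error rests wholly on assumed residual differences of 0.02 to 0.10 SD, assumed ICCs of 0 to 0.05 and a normal approximation with 20 schools. At the low end the problem is negligible. At the high end it would seriously undermine a positive, or a null, Aim 1 result. Because prevention is cheap and later repair is not possible, the change should be made.

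**What to change.** - Keep the enrolment-order list, but do not disclose the HSRC or waitlist condition to the school, agent or recruiters until that school's student roster is consented and, where feasible, its baseline is measured. Hold the mentoring email until the same point.
- Schedule this early in the August to November window.
- Use one arm-neutral recruitment script and flyer in every school.
- Report numbers approached, consented and declined, and baseline characteristics, by arm.
- Limit the Discussion statement to balance at school level.

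The cost is a procedural amendment and neutral recruitment text, with no extra students. The downside is that immediate schools learn their condition, build teams and plan somewhat later. Timing matters. If disclosure waited until November 30, only December 1 to March 31 would remain before the post-test window opens: 31 + 31 + 28 + 31 = 121 days, about 17 weeks including the winter break. At least three programs have to fit in, one of them the 8-week walking challenge, and another listed youth option runs 10 weeks. Roster closure must therefore come early. If a school cannot wait for baseline, concealment until consent is complete still closes the main route, and the neutral materials and counts by arm remain feasible in any case.

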#### HSRC implementer eligibility and recruitment

Extension agents will build an implementation team of 5–10 people to support the HSRC programs at their school (e.g., approval, planning, and/or facilitation of HSRC). The implementation team may include school administrators (e.g., principal, vice-principal, superintendent), classroom teachers, physical activity staff (e.g., physical education teachers), nutrition staff (e.g., school nutrition directors), parent-teacher organization members, volunteers, other Extension agents, student implementers, or any other role that supports HSRC programs (e.g., school health advisory council members). Once Extension agents have built their teams, they will provide the names and contact information to the research staff. The research staff will send study information and an enrollment invitation to all implementation team members, including the Extension agent who formed the team, via email. Adult implementers must be at least 18 years of age and able to speak, read, and write in English to consent. Youth implementers will need a caregiver at least 18 years old to sign a consent form, and they must be able to speak, read, and write in English to participate.

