#### Aim 2 (Implementation) implementation strategy and control conditions

Schools randomized to receive the school-to-school mentoring strategy will participate in a series of activities designed to provide a support system, technical assistance, and facilitate connections between schools concurrently implementing HSRC, as a way to improve implementation outcomes (i.e., acceptability, appropriateness, feasibility). Immediately following randomization to the school-to-school mentoring strategy, participating schools will receive an introductory email welcoming them to the school-to-school mentoring program and informing them about its components (e.g., text messages, newsletters). The research team will host virtual meetings with implementers to discuss implementation successes and barriers. Schools will receive quarterly newsletters (up to four times during the year), which will include a previously recognized HSRC school, links to program implementation resources, a spotlighted HSRC program, and local county health-focused events. For agents who report two or more years of experience with HSRC, we will have them co-lead one monthly mentoring meeting and pair them with less-experienced agents to serve as HSRC mentors. Each month, we will send the Extension agent a reminder email and text message of how much of their $2,000 they have spent and how many programs they have completed. By reminding schools of how much money they have left and where they are in the process of getting the HSRC designation, we will continuously engage them with HSRC. Both the intervention and control groups (i.e., standard implementation) will have access to the HSRC website, which includes research evidence and details for each program, alignment of each program with Texas Essential Knowledge and Skills (TEKS) (i.e., curriculum standards for public schools in Texas), step-by-step instructions on how to earn the HSRC distinction, and additional resources.

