
##### Implementation outcomes

Primary outcomes for evaluating the school-to-school mentoring strategy (aim 2) are acceptability, appropriateness, and feasibility of the HSRC initiative, which we will measure using surveys and interviews. Other outcomes we will measure include the number of students reached and dose delivered. We will also ask implementers to complete a brief survey reporting their sociodemographic characteristics (e.g., biological sex, age, race, ethnicity, school affiliation, and years worked in education).

Acceptability, appropriateness, and feasibility of the HSRC initiative will be assessed among members of each school’s implementation team using three validated instruments: the Acceptability of Intervention Measure (AIM), the Intervention Appropriateness Measure (IAM), and the Feasibility of Intervention Measure (FIM) [58]. Each scale asks respondents to rate their level of agreement with statements about HSRC using a five-point Likert scale ranging from “completely disagree” to “completely agree.” For each measure, we will average item responses to produce a single score between 1 and 5, with higher values indicating more favorable perceptions of HSRC. Surveys will be administered before, during, and after HSRC, allowing us to examine changes in perceptions over time and compare differences between study conditions.

Within 4–6 weeks of the end of HSRC’s implementation, we will conduct interviews at each study school with the Extension agent (n = 20) and at least one other implementer (n = 20). We will use a semi-structured interview guide to ask implementers about the school-to-school mentoring strategy and the overall acceptability, appropriateness, and feasibility of HSRC. The interview guide will also address the five Consolidated Framework for Implementation Research (CFIR) domains – individual characteristics, innovation characteristics (e.g., the HSRC initiative), inner setting (e.g., school characteristics), outer setting (e.g., the community), and implementation process – to determine how the school-to-school mentoring strategy affected each of these domains [59, 60]. Interviews will be conducted in person or online, last 60–90 min, and be recorded.

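### The team that rates the Aim 2 co-primary outcomes is chosen by the Extension agent, with nothing to ensure it is named before mentoring or standard implementation is disclosed

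*Protocol article*

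**What the plan says.** All references are to the protocol article.

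- **Allocation (Randomization).** Each school takes one of four joint conditions, which fix both immediate or waitlist status and mentoring or standard implementation. The order is randomized, and "schools will receive them based on the order in which they enroll in the study (i.e., signed memorandum of understanding").
- **Disclosure (Aim 2 strategy and control conditions).** "Immediately following randomization to the school-to-school mentoring strategy, participating schools will receive an introductory email" that describes the components. Monthly emails and texts go to the agent, and experienced agents act as mentors. Virtual meetings and newsletters also reach other implementers and schools.
- **Choice of raters (HSRC implementer eligibility and recruitment).** "Extension agents will build an implementation team of 5–10 people to support the HSRC programs at their school". The list of roles is open and closes with "or any other role that supports HSRC programs". Then: "Once Extension agents have built their teams, they will provide the names and contact information to the research staff". Research staff invite those people, "including the Extension agent who formed the team".
- **Outcome (Implementation outcomes).** "Acceptability, appropriateness, and feasibility of the HSRC initiative will be assessed among members of each" school's implementation team, by surveys before, during and after HSRC.
- **Analysis (Statistical analysis).** Aim 2 follows the Aim 1 approach: baseline score as covariate, follow-up score as outcome, school as cluster.
- **Students, for contrast (Student eligibility and recruitment).** Student recruitment has a stated time and is said not to depend on the school's condition. The implementer section has no such statement.

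**The concern.** In a cluster trial, randomization protects the comparison of schools. It protects the people measured within schools only if they are identified without regard to the arm. Here one person, who receives the strategy under test and may know the condition, decides how many people join the team and in what roles. That team is the whole rater pool for acceptability, appropriateness and feasibility. If knowing the condition alters who is named or who agrees to take part, a difference between arms can reflect different raters and not a different view of HSRC among comparable raters. People who were never named supply no data, so imputation cannot recover them.

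The Discussion credits randomization with reducing selection bias and strengthening causal inference in both embedded trials. For Aim 2, that holds for the choice of schools but is not secured for the choice of raters.

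**Working it through.** **1. Order of events.** Allocation follows the signed memorandum, and mentoring schools are notified straight afterwards. Team building has no date. No section puts the roster before either event. In the ten waitlist schools, HSRC is delivered a year after the joint condition is assigned, so there is ample time for the condition to be known before a delivery team is formed. That the roster follows disclosure is an inference from these statements, not something the article says.

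**2. The plan's own figure.** The Power analysis gives d = 0.45 (0.25–0.27 points) for 20 schools, 8–10 raters each, ICC 0.015–0.030, type I error 0.05 (taken as two-sided) and power 0.80. With 10 schools per arm and m raters per school:

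DE = 1 + (m − 1) × ICC; d = (1.960 + 0.842) × √(2 × DE / (10m))

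- m = 10, ICC 0.030: DE = 1.27, d = 0.446
- m = 9, ICC 0.015: DE = 1.12, d = 0.442
- m = 8: d = 0.466 (ICC 0.015) and 0.487 (ICC 0.030)

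The stated 0.45 is reproduced for 9–10 raters but not for 8. It serves here only as a scale. The implied SD is 0.25/0.45 = 0.556 to 0.27/0.45 = 0.60; 0.60 is used below.

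**3. Assumed shift in rater mix.** The documents give neither the change in mix nor the score gap between rater types. As an illustration, suppose 20% of team places differ between arms and the two types differ by 0.5 points. The arm means then differ by b = 0.20 × 0.5 = 0.10 points, which is 0.10/0.25 = 40% of the lower detectable difference. A 10% change in mix gives b = 0.05.

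**4. Type I error with no true effect** (two-sided 5% test, normal approximation).

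Unadjusted: SE = 0.60 × √(2 × DE / (10m)), and type I error = 1 − Φ(1.96 − b/SE) + Φ(−1.96 − b/SE).

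Adjusted: assume a baseline correlation of 0.5 and a rater difference that is stable and already present at baseline. The shift falls to b × (1 − 0.5), and SE is multiplied by √(1 − 0.5²) = √0.75.

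| Raters per school | ICC | DE | SE | b = 0.10, unadjusted | b = 0.10, adjusted | b = 0.05, unadjusted | b = 0.05, adjusted |
|---|---|---|---|---|---|---|---|
| 10 | 0.015 | 1.135 | 0.0904 | 19.8% | 9.8% | 8.6% | 6.2% |
| 10 | 0.030 | 1.270 | 0.0956 | 18.2% | 9.3% | 8.2% | 6.0% |
| 5 | 0.015 | 1.060 | 0.1235 | 12.8% | 7.5% | 6.9% | 5.6% |
| 5 | 0.030 | 1.120 | 0.1270 | 12.4% | 7.4% | 6.8% | 5.6% |

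The planned model includes the baseline score, so the adjusted columns are the relevant ones. A t reference with 18 degrees of freedom lowers the unadjusted rates slightly (for example 19.8% to 18.2% at 10 raters, ICC 0.015).

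**The case against.** Four points on the other side carry weight.

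- **Timing.** A reader might infer that the article says agents choose raters after allocation, knowing the arm. It does not. Team building is undated, and the full protocol may fix the roster earlier. What stands is that the sequence as published offers no protection, although the student section does.
- **Mechanism.** The only mentoring component dated to the moment of randomization is a welcome email. The other components run through the year, and none is said to concern choosing team members. Surveys begin before HSRC, so mentoring can do little before the initial team is named. Knowledge of the arm is the more plausible route, and its effect may be small.
- **Direction.** It is tempting to say that the bias favours mentoring on all three outcomes. The documents do not support this: a more engaged agent might equally bring in busier or more sceptical colleagues.
- **Estimand.** If mentoring changes who delivers HSRC, that may be counted as part of its effect, since the views of the actual implementers are what is measured. This is a fair reason to keep later joiners in the main analysis. It does not cover a difference that arises because the agent knew the arm when naming raters.

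Baseline adjustment is also a real mitigation. It takes out part of a stable rater difference, but not all of it, and it does not deal with rater types whose views change differently over time. Finally, the article calls Aim 2 a pilot, which lowers the stakes, although the Discussion claims adequate power for both aims.

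**Conclusion.** The point holds as a gap in safeguards, not as a demonstrated bias. As written, the rater pool for the Aim 2 co-primary outcomes is chosen by a target of the strategy, and nothing ensures that this happens before the condition is disclosed. The arms could differ in rater mix, in a direction that cannot be predicted.

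For an assumed 0.10-point shift, type I error for a single outcome is about 7–10% with the planned baseline adjustment and 12–20% without it, across 5–10 raters per school. For 0.05 points it is about 6% after adjustment, close to nominal. These figures rest on the assumed shift, SD 0.60, the plan's ICC range, and a baseline correlation of 0.5 with a stable rater difference. Quoting the 18–20% found for 10 raters without adjustment as the size of the problem would overstate it, because the plan does adjust. The change is worth making because it is cheap and because analysis cannot fully repair who was invited.

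**What to change.** - Have the agent submit the team roster, with each person's role, before mentoring or standard implementation is disclosed to the agent and school. Send the introductory email after that.
- In waitlist schools, disclose only waitlist status at enrolment. Withhold mentoring or standard until the roster is submitted at the start of the delivery year.
- Invite everyone on the roster. Tabulate rater role and consent by arm, since an early roster protects who is named but not who agrees.
- Add a sensitivity analysis restricted to the pre-disclosure roster and adjusted for role. Later joiners may stay in the main analysis; fixed role slots are not needed.
- If the full protocol already fixes the roster before disclosure, one sentence saying so settles the timing.

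The cost is a short delay to the introductory email and, for waitlist schools, learning the implementation condition later.
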